### **6.3.2 Analysis**

The average PCS and MCS scores will be estimated in each of the groups. These averages will be compared using longitudinal analyses. Linear mixed regression models will be used with the score at each time point as an explanatory variable with constrained longitudinal data analysis. The randomisation arm, the visit, the arm interaction per visit and the centre (adjustment variable) will be used as fixed effects and the patient (intercept + visit) and the surgeon (intercept + group) will be used as random effects. The adjusted mean differences for each score will be derived from these models. The statistical tests will be performed at months 6 and 12.

## **6.4 Number of steps**

### **6.4.1 Definition**

The number of steps is assessed every day of the week following the enrolment visit and every day of the week before the other visits (preoperative visit, week 6, month 3, month 6 and month 12). The average daily number of steps over the 7 days will be calculated for each visit.

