#### **1st session: physical exercise before the arthroplasty.**

The role of physical exercise on health and participation, which exercises to do while awaiting surgery, when and how to do them when you return home.

We will confirm that the pedometer is used properly (Annex 10). For active patients, the aim will be to maintain the level of activity. For sedentary patients, the aim will be to gradually increase the number of steps measured using a pedometer by 20% before the surgery. This session is led by a physiotherapist or a sports instructor.

At the end of this session, the physiotherapist will give the patients the self-exercise programme to be done at home.

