## **VI.2 - SECONDARY ENDPOINTS**

### **Efficacy criteria**

At 6 months and 12 months:

- The average change from baseline in the average knee pain intensity in the past 48 hours, assessed using a self-administered 11-point numeric scale (0 = no pain and 100 = maximum pain)
- The average change from baseline in the average function assessed using the area under the curve of the function subscale of the WOMAC index (0 = best possible function and 100 = worst possible function)
- The average change from baseline in the average quality of life assessed using the physical and psychological components of the MOS SF-12 score (0 = worst possible quality of life and 100 = best possible quality of life) and using the EQ-5D-3L score (1111 = best possible quality of life and 33333 = worst possible quality of life)
- The average change from baseline in the average self-reported number of steps in the past week, measured using a pedometer.
- The average treatment satisfaction assessed using a self-administered 11-point numeric scale (0 = zero satisfaction and 100 = maximum satisfaction).
- The cost-effectiveness assessed using the cost-effectiveness ratio.

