| Length of stay at rehabilitation care facilities   |                 |                         |                               | +                  | +                      |                    | +(a)          |                         |
| MOS SF 12                                          | +               | +                       |                               |                    | +                      |                    | +             | +                       |
| EQ-5D-3L                                           | +               |                         |                               |                    |                        |                    | +             | +                       |
| RAPT                                               | +               |                         |                               |                    |                        |                    |               |                         |
| Adaptation to environment                          |                 | +                       |                               |                    | +                      |                    |               |                         |
| Number of steps                                    | +(b)            | +(c)                    |                               |                    | +(c)                   |                    | +(c)          | +(c)                    |
| Treatment satisfaction                             |                 |                         |                               |                    |                        |                    | +             | +                       |
| Co-interventions                                   | +               | +                       |                               |                    | +                      |                    | +             | +                       |
| Adverse Events                                     |                 | +                       | +                             |                    | +                      |                    | +             | +                       |

(a) If the length of stay is longer than 6 weeks

(b) To be performed the week after the enrolment visit (7 days)

- (c) To be performed the week before the enrolment visit (7 days)

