## **VII.1 - VISIT V0 - ENROLMENT VISIT**

The patients selected within the surgical department at Clermont-Ferrand University Hospital and Lariboisière and Cochin hospitals will be contacted by the clinical study technician and, if they are potentially interested in the study, they will be referred to the PMR departments at Cochin and Clermont-Ferrand and the Lariboisière rheumatology department for their enrolment visit and their study follow-up.

At the enrolment visit, the rehabilitation physician or the rheumatologist, with the help of the clinical study technician, will systematically confirm the inclusion and exclusion criteria. The study methods will be clearly explained to the patient. The patient will be given an information sheet and informed consent form. If the patient agrees to take part in the study, he or she will sign the informed consent form.

The following information will be collected in the electronic case report form:

- Demographic parameters (age, sex);
- Socioprofessional parameters (level of studies, profession and professional status (working, on sick leave, on disability, retired));
- Medical examination (weight, height and BMI);
- Inclusion and exclusion criteria;
- Information and consent;
- Demonstration of how to use the pedometer to measure the number of steps taken in the week after the enrolment visit;
- Co-interventions (particularly analgesics and/or NSAIDs, physiotherapy).

Patients will fill in a self-assessment card during the visit, including assessment of the following:

- knee pain over the past 48 hours, assessed using a visual numeric scale from 0 to 100;
- preference regarding hospital discharge destination and RAPT scale (Annex 6);
- function according to the WOMAC scale and the personalised section;
- quality of life (MOS SF-12, Annex 4 and EQ-5D-3L, Annex 5).

The time elapsed between the enrolment visit and the start of the multidisciplinary programme will be no more than one month.

**Randomisation:** patients will be randomised using CleanWeb software.

After randomisation, the patients in the two arms will receive a copy of the Knee Arthroplasty Guide (Annex 11).

The patients randomised into the “standard-treatment” control arm will receive standard medical care.

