### **6.4.2 Analysis**

The average number of steps will be estimated in each of the groups. These averages will be compared using a longitudinal analysis. A linear mixed regression model will be used with the score at each time point as a response variable with constrained longitudinal data analysis. The randomisation arm, the visit, the arm interaction per visit and the centre (adjustment variable) will be used as fixed effects and the patient (intercept + visit) and the surgeon (intercept + group) will be used as random effects. The adjusted mean differences will be derived from this model. The statistical tests will be performed at months 6 and 12.

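### The baseline week of pedometer steps follows unblinded randomisation, so the equal-baseline assumption of the steps model is not protected by the design

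*Supplement*

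**What the plan says.** **Timing of the first record.** SAP 6.4.1: "The number of steps is assessed every day of the week following the enrolment visit". Protocol VII.1 agrees. What happens at V0 is "Demonstration of how to use the pedometer to measure the number of steps taken in the week after the enrolment visit". Footnote (b) to the protocol's schedule of assessments says the same.

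**Randomisation and blinding.** Protocol III.4 and VII.1 place consent and randomisation at the enrolment consultation. Protocol III.3 says that patients cannot be blinded.

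**Start of the programme.** Protocol VII.1: "The time elapsed between the enrolment visit and the start of the multidisciplinary programme will be no more than one month". No minimum interval is given. Session 1 concerns physical activity and checks pedometer use. Protocol V.1 adds: "For sedentary patients, the aim will be to gradually increase the number of steps measured using a pedometer by 20% before the surgery". Active patients are asked only to maintain their level.

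**Analysis.** SAP 6.4.2 fits a linear mixed model "with the score at each time point as a response variable with constrained longitudinal data analysis", with arm, visit, arm-by-visit and centre as fixed effects and tests at months 6 and 12. Protocol VI.2 defines the endpoint as "The average change from baseline in the average self-reported number of steps in the past week".

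By contrast, enrolment pain, WOMAC, SF-12 and EQ-5D are completed during V0 itself.

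**The concern.** A constrained longitudinal analysis gives both arms the same mean at the first time point. Randomisation justifies this for a value measured beforehand. It gives no such guarantee for a value measured afterwards in patients who may know their arm, some of whom may already have attended a session aimed at walking. Steps are the only repeated outcome in this position, yet they receive the same model as the others.

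If the arms already differ in that week, the model reads the difference as chance imbalance and corrects for it. A change score subtracts all of it. Number of steps at 6 and 12 months is a stated secondary objective, and physical activity is a behaviour that the programme sets out to change. Neither document plans a sensitivity analysis for this.

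**Working it through.** The plan gives no sample size, mean, SD or correlation for steps, so there is no stated figure to reproduce. The check concerns the mechanism and its plausible size.

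**1. Formula.** Let D0 (called d elsewhere) be the arm difference in the post-V0 week and Dt the difference at month t. With a common first-visit mean imposed, the estimate tends to

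Dt - b x D0, where b = cov(Y0, Yt) / var(Y0).

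With equal SDs, b = r. The shift is therefore -r x D0, and for a change score -D0. Writing f = D0/Dt, the constrained model keeps a share 1 - r x f of the true effect and a change score keeps 1 - f. Both f and r are assumptions.

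| f | r = 0.3 | r = 0.5 | r = 0.7 | change score |
|---|---|---|---|---|
| 0 | 100% | 100% | 100% | 100% |
| 0.25 | 92.5% | 87.5% | 82.5% | 75% |
| 0.5 | 85% | 75% | 65% | 50% |
| 1 | 70% | 50% | 30% | 0% |

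**2. Simulation.** Two time points, known covariance, 150 per arm, 2,000 runs per setting, true later effect 0.40 SD. With f = 0.5 the mean estimates were 0.341, 0.304 and 0.261 for r = 0.3, 0.5 and 0.7 (theory 0.34, 0.30, 0.26). With f = 0 they were 0.398, 0.402 and 0.395, so there is no bias when nothing has happened by that week.

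**3. Overlap with session 1.** Assume session 1 falls uniformly over days 0-30 after V0. The chance that it falls in the 7-day record is 7/30 = 23%. The share of intervention-arm step-days that follow it is 7/30 x 1/2 = 12% (13% counting whole days).

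**4. Size from overlap alone.** Suppose, generously, that every patient is sedentary and reaches half of the 20% aim at once. Then D0 is about 12.5% x 10% = 1.25% of mean steps. With r = 0.5-0.7 the shift is 0.5 x 1.25% to 0.7 x 1.25%, or about 0.6-0.9% of mean steps (1.25% for a change score). Any effect of knowing the allocation is extra, may have either sign, and cannot be quantified from the documents.

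**5. Cost of discarding the first week.** Adjustment for it removes r-squared of the variance: 25% at r = 0.5 and 49% at r = 0.7. Without it, the same precision needs 1/(1 - 0.25) = 1.33 to 1/(1 - 0.49) = 1.96 times the patients, before any recovery from other covariates. With n = 150 per arm, in SD units:

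- planned model, mean squared error: (1 - r^2) x 2/n + r^2 x D0^2
- unadjusted comparison: 2/n

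The planned model is better when D0 < sqrt(2/150) = 0.115 SD. For D0 = 1.25% of the mean, this holds for any step SD above 1.25/0.115 = 11% of the mean.

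**The case against.** The strongest reply is that the timing is conceded but little follows from it.

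- **Only an early difference matters.** The intended mechanism acts through the sessions and the weeks after them. Both arms receive a pedometer and are taught to use it, so reactivity to the device is common to both. No section says exactly when patients learn their arm. This stands: the sign and size of d are unknown.
- **Early overlap should be limited.** The 20% aim is gradual and for sedentary patients only. Sessions run in groups of 4 to 6, arranged by a later contact. With 300 patients over 45 months at 3 sites, a site of average size randomises about 300/45/3/2 = 1.1 intervention patients a month. At the hoped-for 160 a year it is 160/12/3/2 = 2.2. Filling a group of four takes roughly 2 to 4 months, so week-one starts should be uncommon. This largely stands, although a patient who completes a group could start at once and nothing forbids it.
- **The model may not be constrained.** SAP 6.4.2 also lists an arm main effect. Fitted literally, the first-week means are free and the month 6 and 12 contrasts are not shifted. This shows that the text is ambiguous, not that the analysis is safe: the SAP names the constrained method.
- **Replacing the model could do harm.** The precision given up may exceed the bias removed. This stands against dropping the planned analysis, but not against a sensitivity analysis.

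A reader might infer that part of any programme effect on steps is removed, or that the loss is a few per cent of mean steps. The second needs, for example, half the intervention arm at half the aim throughout the week (0.5 x 0.5 x 20% = 5%, hence 2.5-3.5% at r = 0.5-0.7). The documents support neither reading.

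**Conclusion.** The point holds as a design weakness in one secondary outcome. The first step week is post-randomisation, patients are unblinded, session 1 may fall inside it, and both the constrained model and the change-from-baseline definition treat it as a pre-treatment value.

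The resulting shift is about -r x d, or -d for a change score, where d is whatever difference already exists in that week. If d favours the intervention, the effect is understated; if it favours control, it is overstated; if d is zero, nothing is lost. On the assumptions shown, overlap alone would give less than 1% of mean steps under the constrained model. The contribution of knowing the allocation is unknown. The equal-SD form, the range of r and the uniform start date are all assumptions. Neither primary endpoint is touched, and the case for acting rests on how cheap the repair is.

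**What to change.** **While enrolment is open.** In protocol VII.1, require the 7-day pedometer record to be complete before allocation is disclosed and before session 1. The technician already contacts intervention patients after V0 to arrange sessions. The cost is up to one week of the existing one-month window.

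**For data already collected.** Amend SAP 6.4.2 as follows:

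- Keep the planned model, and state whether the arm effect at the first step week is constrained to zero.
- Add a sensitivity analysis of steps at months 6 and 12 that treats the post-V0 week as a post-randomisation time point with its own arm effect, with no constraint and no change score, adjusted for covariates completed at V0 (enrolment WOMAC function, age, BMI).
- Report the time from V0 to session 1 in the intervention arm.

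The cost is a little more analysis work and lower precision in the sensitivity analysis, which is why it should accompany the planned model rather than replace it.

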### **6.4.2 Analysis**

The average number of steps will be estimated in each of the groups. These averages will be compared using a longitudinal analysis. A linear mixed regression model will be used with the score at each time point as a response variable with constrained longitudinal data analysis. The randomisation arm, the visit, the arm interaction per visit and the centre (adjustment variable) will be used as fixed effects and the patient (intercept + visit) and the surgeon (intercept + group) will be used as random effects. The adjusted mean differences will be derived from this model. The statistical tests will be performed at months 6 and 12.

## **6.5 Treatment satisfaction**

### **6.5.1 Definition**

Treatment satisfaction is assessed at month 6 and month 12 with a score ranging from 0 to 100.

### **6.5.2 Analysis**

The average treatment satisfaction scores will be estimated in each of the groups. These averages will be compared using a longitudinal analysis. A linear mixed regression model will be used with the score at each time point (month 6 and month 12) as the response variable. The randomisation arm, the visit, the arm interaction per visit and the centre (adjustment variable) will be used as fixed effects and the patient (intercept + visit) and the surgeon (intercept + group) will be used as random effects. The adjusted mean differences will be derived from this model. The statistical tests will be performed at months 6 and 12.

## **7 Tolerance analysis**

### **7.1 Adverse events**

#### **7.1.1 Definition**

Any adverse events spontaneously reported by patients at telephone follow-up visits or recorded at a visit will be taken into account. The following information will be collected for each adverse event:

- its intensity (severity): mild, moderate or severe;
- its treatment, if any;
- its duration;
- its causality, as determined by the investigator (not assessable, unlikely, possible, likely, certain, or unrelated to the investigational treatment).

The adverse event rate will be analysed at month 12.

#### **7.1.2 Analysis**

Adverse events and their characteristics will be described in the form of sample sizes and percentages by treatment arm. Fisher's exact tests will be used to compare the two treatment arms in terms of the proportion of patients with at least one AE/SAE and the proportion of patients with at least one SAE. The total number of AEs/SAEs and SAEs will also be described for each arm.

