### **3. Secondary endpoint analysis**

The long-term analysis of the quantitative efficacy criteria repeated over time (personalised WOMAC, numeric pain scale, SF12, number of steps, satisfaction) will be carried out using a linear mixed model for repeated measurements (MMRM) taking into account the correlation of the measurements repeated in the same subject (random effect). The fixed effects will be the randomisation arm, operator, time, initial endpoint value and interaction between the time and the randomisation arm. The model will therefore allow us to compare the means adjusted to the absolute variations between the different times of interest (preoperative, 6 months, 1 year) and the initial visit. This analysis technique is consistent with the principle of the intention-to-treat analysis provided that all patients have a baseline value reported for the endpoint.

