## **X.2 - DESCRIPTION OF THE SAFETY ASSESSMENT PARAMETERS**

The study-specific procedures are as follows:

- 4 exercise sessions;
- 4 therapeutic education sessions;
- preoperative assessment;
- daily assessment of discharge ability from D1 to D5;
- self-exercise programme and DVD;
- follow-up questionnaires at 6 weeks, 4, 5 and 6 months (by post, email or telephone).

This is a multidisciplinary programme combining therapeutic education and exercises, with the exercise intensity being adapted to the patient's pathology and age, under the supervision of a physiotherapist. We have no known or reported factors regarding the risks related to the education programme.

The adverse events that may occur during the study are mainly related to the assigned treatment strategies.

- Main adverse events related to the education programme
  - ✓ no known or reported evidence on this subject
- Main adverse events related to the exercise programme
  - ✓ increase in exercise-related pain

- ✓ exercise-related injuries to muscles (cramps, elongation), ligaments (sprain) and joints (effusion). These are minor, non-progressive injuries which are quick to heal, as the exercise intensity will be adapted to the patient's pathology and age, under the supervision of a physiotherapist.

If any events occur, the patients will be assessed by the doctor in charge of the study for their treatment.

The study doctor will record adverse events (AEs) from the date on which the informed consent form is signed, for the whole duration of the patient's participation in the study, on the adverse events page of the case report form.

As this is a biomedical research study classified as "risk A", i.e. for which there is a negligible **additional risk expected for the study**, no **serious** adverse events are expected through the course of the study.

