#### **6.1.2 Analysis**

The average pain assessment will be estimated in each of the groups. These averages will be compared using a longitudinal analysis. A linear mixed regression model will be used with assessment of pain at each time point (enrolment visit, preoperative visit, week 6, month 3, month 4, month 5, month 6 and month 12) as an explanatory variable with constrained longitudinal data analysis. The randomisation arm, the visit, the arm interaction per visit and the centre (adjustment variable) will be used as fixed effects and the patient (intercept + visit) and the surgeon (intercept + group) will be used as random effects. The adjusted mean differences will be derived from this model. The statistical tests will be performed at months 6 and 12.

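### SAP 7.1 tests adverse events only cumulatively to month 12, which dilutes the preoperative harms that the protocol names

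*Supplement*

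**What the plan says.** SAP 7.1.1 defines what is counted: "Any adverse events spontaneously reported by patients at telephone follow-up visits or recorded at a visit will be taken into account". It fixes one analysis time: "The adverse event rate will be analysed at month 12". For each event it lists intensity, treatment, duration and investigator-assessed causality. An onset date is not in that list.

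SAP 7.1.2 plans two between-arm tests. In the first, "Fisher's exact tests will be used to compare the two treatment arms in terms of the proportion of patients with at least one AE/SAE"; the second takes "the proportion of patients with at least one SAE". Event characteristics and total AE and SAE counts are described by arm. Nothing is split at surgery, by type of event, or by relation to the programme.

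Protocol X.2 opens the recording window early: "The study doctor will record adverse events (AEs) from the date on which the informed consent form is signed", and keeps it open for the whole of participation. The same section names the risks of the exercise programme: more exercise-related pain, and "exercise-related injuries to muscles (cramps, elongation), ligaments (sprain) and joints (effusion"). It calls these injuries minor and quick to heal, and knows of no risks from the education part. The schedule of assessments and protocol VII.3.1 collect AEs in both arms at the preoperative visit (V1), one or two days before surgery.

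On pain, protocol IX.4 (secondary endpoint analysis) refers to "the different times of interest (preoperative, 6 months, 1 year"). SAP 6.1.2 includes the preoperative visit in the model, but says "The statistical tests will be performed at months 6 and 12".

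**The concern.** The programme consists of four supervised sessions and then home exercise until the arthroplasty. Its named harms therefore arise before surgery. Both arms then undergo the same major operation and are followed for 12 months, during which AEs unrelated to the programme accrue in each. In a count of patients with at least one AE, a programme patient with an exercise injury and a later postoperative event scores the same as a control patient with the postoperative event alone. The preoperative excess is partly hidden, although AEs at V1 would let it be seen.

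At stake is how well the final analysis can speak to tolerance. Protocol X.4.2 plans no independent monitoring committee, so the final comparison is the main between-arm look at harm. Neither primary endpoint is touched.

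**Working it through.** **No figure to reproduce.** The documents give no expected AE rate, power or detectable difference for the safety comparison. The rates below are assumptions, shown over a range.

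**Inputs**
- 150 patients per arm (protocol IV.3).
- Two-sided tests (SAP 4.1). That section sets 2.5% for the primary endpoints and 5% for the secondary endpoints, and names no threshold for safety; 5% is assumed.
- Assumed preoperative AE risk: 10% in the programme arm and 2% in the control arm, that is 150 × 0.10 = 15 v 150 × 0.02 = 3 patients. A second scenario uses 15% v 5%.
- Assumed postoperative AE risk: equal in the two arms and independent of preoperative events, from 5% to 70%.

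**Formula.** Cumulative risk in an arm = 1 − (1 − pre)(1 − post). The visible difference is therefore (1 − post) × (pre in programme arm − pre in control arm). With post = 30%, the programme arm has 1 − 0.90 × 0.70 = 37.0% and the control arm 1 − 0.98 × 0.70 = 31.4%. The difference is 5.6 points instead of 8.

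**Power.** Exact power of the two-sided Fisher test, summed over the two binomial distributions:

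| Postoperative AE risk | Difference, 10% v 2% (points) | Power, 10% v 2% | Power, 15% v 5% |
|---|---|---|---|
| none (preoperative window only) | 8.0 | 80.2% | 79.7% |
| 5% | 7.6 | 51.0% | 59.5% |
| 10% | 7.2 | 34.9% | 45.4% |
| 20% | 6.4 | 21.2% | 29.6% |
| 30% | 5.6 | 14.5% | 20.4% |
| 50% | 4.0 | 9.5% | 12.4% |
| 70% | 2.4 | 5.8% | 7.1% |

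Most of the loss comes from added noise rather than from the smaller difference: at 10% postoperative risk the difference has fallen only from 8.0 to 7.2 points, but power has more than halved.

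**Sensitivity to sample size.** Protocol IX.2 expects about 10% losses before the procedure and needs 130 per arm. Take events in 10% of the programme arm and, before surgery, none in the control arm. Power then falls from 99.2% to 27.9% at a 20% background with 130 per arm, and from 99.8% to 32.2% with 150.

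**The SAE test.** The named injuries are described as minor, so few would meet the definition of a serious event in protocol X.1. The second Fisher test does not fill the gap.

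**The case against.** The strongest reply is that the tolerance plan is wider than one Fisher test. There is a separate SAE test, and event characteristics, including causality, are tabulated by arm. Events attributed to the programme could therefore be seen. This stands as far as it goes. But a description is not a comparison, and protocol III.3 concedes that the medical team cannot be blinded. Causality is also rated against a treatment that control patients did not receive.

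A reader might infer that the named harms are bound to be swamped and the comparison worthless. The documents do not support that, because they give no postoperative AE rate. The rate could be low: events are captured by spontaneous report or at visits, and the contacts at 6 weeks and at 4 and 5 months list no AE item. A large excess would also survive moderate dilution: with events in 20% of the programme arm and none before surgery in controls, power is 84.9% at a 20% background, though 52.4% at 40%. What stands is that for smaller excesses the loss is already marked at a 5% to 10% postoperative risk.

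A reader might also infer that the SAP ignores preoperative pain. It does not. The model in 6.1.2 holds the preoperative visit and the arm-by-visit term; only testing is confined to months 6 and 12, in line with the stated pain objective. Nor is that score a full measure of exercise harm. It covers the 48 hours before a visit held one or two days before surgery, whereas the sessions begin at least two months before surgery.

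Finally, the SAP nowhere says that a non-significant test will be reported as absence of harm. The study is classed as risk A, with no serious adverse events expected.

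**Conclusion.** The point holds as a limited one. The planned between-arm AE tests are cumulative to month 12, and the programme's named risks are preoperative and minor. The AE test is therefore diluted by events common to both arms, and the SAE test is aimed elsewhere. That structure is clear from the documents. The size is not: it rests on assumed risks, on independence of preoperative and postoperative events, and on equal postoperative risk in the two arms. Under 10% v 2%, power falls from 80.2% to between 51.0% and 9.5% as postoperative risk goes from 5% to 50%.

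It would be tempting to make the preoperative window the main tolerance test. The documents do not support that either. Before surgery the programme arm has four supervised sessions and a weekly exercise diary (protocol VII.2), while no matching control contact is scheduled between enrolment and V1. Part of any excess could be better ascertainment. Splitting at surgery is a cheap improvement to reporting, not the repair of a fault that threatens the trial's main conclusions.

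**What to change.** In SAP 7.1.2, keep the cumulative analysis and add two rows: the number and proportion of patients with at least one AE, by arm, with a confidence interval for the difference, for (a) consent to V1 and (b) surgery to month 12. State the denominator for each window, since losses before the procedure are expected, and say where events in the one or two days between V1 and surgery are counted. Report from the model in 6.1.2 the adjusted arm difference in pain at the preoperative visit with its confidence interval.

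No new data are needed for a split at surgery: AEs are collected at V1, and protocol VIII.2 requires visit dates in the case report form. A finer division is not assured, because SAP 7.1.1 lists no onset date.

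The costs are SAP wording, a few table rows and a few extra descriptive comparisons. The SAP should also state that the programme arm may over-report before surgery because of its sessions and diary, and that the preoperative comparison is descriptive.
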